**Methods:**

The AMETHIST intervention (Adapted Microplanning to Eliminate Transmission of HIV in Sex Transactions) is a risk-differentiated intervention for FSW, centred around the implementation of microplanning and self-help groups. It is designed to support uptake of, and adherence to, HIV prevention, testing and treatment behaviours among FSW. Twenty-two towns in Zimbabwe were randomised to receive either the Sisters programme (usual care) or the Sisters programme plus AMETHIST. The composite primary outcome is defined as the proportion of all FSW who are at risk of either HIV acquisition (HIV-negative and not fully protected by prevention interventions) or of HIV transmission (HIV-positive, not virally suppressed and not practicing consistent condom use). The outcome will be assessed after 2 years of intervention delivery in a respondent-driven sampling survey (total *n* = 4400; *n* = 200 FSW recruited at each site). Primary analysis will use the ‘RDS-II’ method to estimate cluster summaries and will adapt Hayes and Moulton’s ‘2-step’ method produce adjusted effect estimates. An in-depth process evaluation guided by our project trajectory will be undertaken.

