### Analysis principles

Our primary analysis will compare FSW recruited in each community without considering direct contact with the intervention components (i.e. an ‘intention to treat’ approach). Data from individual FSW will be summarised for each cluster, and we will express the intervention effect using a prevalence ratio, prevalence difference and associated 95% confidence intervals.

We will calculate cluster summaries using the RDS-II methodology [31]. For unadjusted analysis, we will fit a linear regression model on the RDS-weighted cluster summaries, with a treatment dummy. We will use the *p*-value and confidence intervals for the coefficient of the treatment dummy.

Adjusted analysis will use the ‘two step’ method of Hayes and Moulton [32]. Age is specified a priori and will be included as a potential confounder that could affect the outcome. We will also adjust for other potential confounders that appear imbalanced by arm between survey participants recruited to the endline RDS surveys. Imbalance will be assessed using ‘eyeballing’ and expert opinion. Decisions about factors to be adjusted for will be made prior to the analysts having access to the complete primary outcome data. We will not adjust for any characteristics that may have been influenced by the intervention. To generate adjusted and RDS-II-weighted analysis, step 1, we fit a logistic regression model for each site with the primary outcome as the dependent variable, age and other variables as independent variables. This model will be used to ‘predict’ outcomes for each woman. The predicted values will be multiplied by the inverse of the degree (RDS-II) to account for the sampling design, normalised for the cluster, and cluster summaries calculated. Step 2, we will divide the cluster summaries used in the unadjusted analysis (accounting for RDS only) by the adjusted cluster summaries from step 1 to generate ‘residuals’. We will calculate the prevalence ratio using the regression model described above with the residuals as the dependent variable. We will calculate the ‘residual’ risk difference (RD) by subtracting the predicted prevalence from the RDS-II weighted observed prevalence in each cluster. We will fit a linear regression model on the residuals to calculate the adjusted RD and 95% confidence intervals.

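### As written, step 1 of the adjusted analysis fits a separate model in each site, so the adjusted estimate is driven towards no effect; one model across all sites is needed

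*Protocol article*

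**What the plan says.** The section 'Analysis principles' of the protocol article names the two-step method for the adjusted analysis and then spells it out.

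- Model: "step 1, we fit a logistic regression model for each site with the primary outcome as the dependent variable, age and other variables" as predictors.
- Prediction: "This model will be used to ‘predict’ outcomes for each woman".
- Weighting: "The predicted values will be multiplied by the inverse of the degree (RDS-II) to account for the sampling design", followed by normalisation within the cluster. No weights are mentioned for the fit itself.
- Ratio residual: "we will divide the cluster summaries used in the unadjusted analysis (accounting for RDS only) by the adjusted cluster summaries from step 1".
- Difference residual: "subtracting the predicted prevalence from the RDS-II weighted observed prevalence in each cluster".
- Test: a linear regression of the cluster residuals on a treatment dummy.

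The unadjusted analysis in the same section regresses the RDS-II weighted cluster summaries on arm directly. The abstract describes the primary analysis as RDS-II cluster summaries together with an adaptation of the two-step "method produce adjusted effect estimates". No part of the article says that the step 1 model is fitted once across all sites.

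**The concern.** The two-step approach compares what was observed in a cluster with what its covariate mix alone would lead one to expect. The expectation has to come from a model that does not know the cluster's own level. A model fitted inside one site does know it, because its intercept is estimated from that site's outcomes. All women in a site belong to the same arm, so the intercept also carries the intervention effect. Dividing by the prediction, or subtracting it, then removes the effect along with the covariate differences.

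The result would not look like a failed model. It would look like a fairly precise null, standing beside an unadjusted estimate that might show a clear effect. Changing the model after seeing that contrast would be a post hoc change to part of the primary analysis.

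**Working it through.** **Inputs from the article** ('Sample size and power considerations'): 22 clusters, so 11 per arm; about 200 women each; control prevalence 30%; k of 0.20 (0.25 also considered); relative reductions of 30% and 50%, i.e. PR 0.70 and 0.50.

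**Check of these inputs.** The article gives no figure for the adjusted analysis itself, only power. By the Hayes-Bennett formula with k = 0.20, the variance term is 0.30×0.70/200 + 0.21×0.79/200 + 0.20²×(0.30² + 0.21²) = 0.00105 + 0.00083 + 0.00536 = 0.00724. Then 0.09×√(10/0.00724) − 1.96 = 1.38, which is 91.7% power. This agrees with the stated 90% in most scenarios.

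**Algebra.** For woman i in site j, let y be the outcome and p̂ the step 1 prediction. A logistic model with an intercept satisfies Σ(y − p̂) = 0 over the data it is fitted to. Fitted within site j, mean predicted equals mean observed in that site.

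With w = 1/degree, the cluster residual is O − E = Σw(y − p̂)/Σw. There are two cases:

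1. Neither fit nor summaries weighted, or both carrying the same weights: O − E = 0 exactly, so O/E = 1 in every cluster.
2. Unweighted fit with weighted predictions, which is the order in the text: O − E = cov(w, y − p̂)/mean(w), taken within the site. This depends on how degree relates to the outcome inside the site, not on the site's level. The intervention effect has already gone.

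**Two-site illustration.** Take equal covariate mixes and ignore weights: a control site with 60/200 (30%) and an intervention site with 42/200 (21%).

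- Per-site models: E = 30% and 21%, so O/E = 1 and 1. PR = 1 and RD = 0.
- One model over both sites: E = 102/400 = 25.5% in each. O/E = 0.300/0.255 = 1.176 and 0.210/0.255 = 0.824. PR = 0.824/1.176 = 0.70 and RD = −0.045 − 0.045 = −0.09.

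**Simulation.** 200 trials per row with the inputs above and k = 0.20. Assumed, because the article does not give them: age slope −0.3 log-odds per SD; skewed degree with mean about 10; degree either unrelated to the outcome or with slope −0.3 log-odds per log degree. Residuals were formed in the text's order and compared by a t-test on 20 df. Entries are median PR / mean RD / rejection.

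| True PR | Degree predicts outcome | Unadjusted | Per-site model | One pooled model without arm |
|---|---|---|---|---|
| 0.70 | no | 0.695 / −0.091 / 85% | 0.999 / −0.000 / 6% | 0.696 / −0.091 / 85% |
| 0.70 | yes | 0.704 / −0.104 / 87% | 1.013 / −0.011 / 8% | 0.707 / −0.104 / 87% |
| 0.50 | no | 0.494 / −0.151 / 100% | 0.991 / −0.002 / 5% | 0.494 / −0.151 / 100% |
| 0.50 | yes | 0.518 / −0.168 / 100% | 1.038 / −0.019 / 9.5% | 0.520 / −0.168 / 100% |
| 1.00 | no | 1.004 / 0.001 / 3% | 0.997 / −0.001 / 3.5% | 0.999 / 0.001 / 3.5% |
| 1.00 | yes | 1.000 / −0.002 / 3% | 0.995 / −0.001 / 2.5% | 0.998 / −0.002 / 3% |

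The Monte Carlo standard error is about 2.5 points at 85% (√(0.85×0.15/200)). Further runs with other assumed age and degree effects gave, at true PR 0.70, per-site PRs of 1.00 to 1.02 with 5-9% rejection, and pooled PRs up to 0.73 with about 86%. In a 400-trial run at true PR 0.70 the per-site 95% CI for the PR averaged 0.91 to 1.09, against 0.55 to 0.89 with the pooled model.

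**Size of the gaps in case 2.** At true PR 0.70 the mean absolute difference between observed and predicted prevalence was 2.6 points, or 4.8 points when degree predicts the outcome.

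**The case against.** The strongest reply is that the phrase about each site is loose wording. The two-step method is named, the next sentence speaks of one model in the singular, and normalising by cluster follows. The authors may have meant one model with predictions summarised by site. The section also says the approach follows a previously published analysis, and the full protocol is not shown. It stands that intent cannot be settled from this article. But the abstract says the method is adapted, so its name does not override an explicit step. The article's 'RDS diagnostics' section also uses the same phrase to mean site by site.

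Three stronger readings are tempting, and the documents do not support them.

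- A reader might infer that predicted equals observed exactly in every cluster. That needs matching weights in fit and summaries. The text weights only the predictions, so gaps of a few points remain.
- A reader might infer that the inverse-degree step adds only noise. If degree predicts the outcome, a small systematic remainder is left: RD −0.011 at true PR 0.70 and −0.019 at 0.50 in the table, with rejection up to 20% at PR 0.50 in one further run. This is still far from the true effect, and in those table rows the PR lies slightly above 1 while the RD is negative.
- A reader might infer that the whole primary analysis is lost. The unadjusted RDS-II comparison is intact, and 'Analysis principles' does not rank the adjusted result above it. A conflict between the two would also be a visible warning.

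**Conclusion.** The point holds on the text as written. A separate step 1 model per site removes nearly all of any intervention effect from the adjusted PR and RD. At a true PR of 0.70 the adjusted PR is 1.00 to 1.02 with 5-9% rejection, against about 0.70 to 0.73 and 85-87% from one pooled model. Even a halving of risk leaves the per-site PR between 0.99 and 1.04 in the tabulated runs.

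The loss of the effect follows from algebra. The exact figures rest on assumed age and degree effects. The damage is confined to the adjusted estimate, which the abstract counts within the primary analysis. If the third sensitivity analysis (no RDS weighting) were applied to the adjusted estimate with per-site models, every ratio would be exactly 1 and no test would exist. Whether the trial would really be analysed this way cannot be known from the article; the finding is that the published steps, followed literally, do not work.

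**What to change.** In 'Analysis principles', replace the per-site fit with wording such as: *fit a single logistic regression to all women in all 22 sites, with age and the covariates selected under the stated imbalance rule, without a treatment term and without site effects.* Site effects must be left out because site-specific intercepts would bring the same problem back.

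Refer to the existing imbalance rule rather than to pre-specified covariates. Only age is fixed in advance; the others are chosen before the analysts have the complete primary outcome data.

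Add whether this fit is RDS-II weighted. The weighted expected prevalence, the ratio residuals and the difference residuals per cluster can then be formed as already described.

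The cost is about one sentence, with no new data and no change to the outcome or sample size. If a single model was always intended, the edit only makes the text say so. It should be in place before the adjusted results are seen.

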### Sensitivity analysis

To investigate robustness of our primary effect estimate, we will conduct sensitivity analyses in which we (1) re-calculate the primary effect only in FSW who enrolled in AMETHIST intervention compared with individually matched controls, (2) re-calculate the primary effect only in FSW who have been in contact with the Sisters programme, (3) re-calculate the primary effect estimate using cluster-summaries unadjusted for RDS-II methodology (without weighting) and (4) re-calculate the estimated effect using the ‘Successive Sampling’ estimator (‘RDS-SS’), designed to avoid the with-replacement assumption in the random walk model. RDS-SS requires estimates of the population size of FSW to already be available [33]. We will also conduct RDS-SS analyses for a range of possible population sizes [33] and assess whether findings differ using these estimates.

## Discussion

We describe the intervention, rationale, trial design and analysis plan for a pragmatic cluster randomised trial conducted within the Sisters programme in Zimbabwe of a complex intervention combining microplanning and self-help groups to support the uptake of and adherence to HIV prevention and treatment interventions for female sex workers.

We have adapted approaches found to be effective in other contexts in building community capacity to reduce vulnerability to, and improve management of, HIV infection. First, microplanning formalises peer outreach activities into a series of specified activities that engage FSW at each stage, i.e. mapping hotspots, identifying local sex workers, conducting routine risk assessments and collecting and analysing data with support from outreach workers [34]. This process allows for greater flexibility and local responsiveness of HIV programmes delivered at scale, and further consolidates FSWs leadership and ownership over the programme [35]. Second, the empowerment workers, in the AMETHIST intervention, are given further responsibility for bringing groups of 10–15 FSW together into self-help groups where they can discuss shared concerns, provide group support and eventually take collective action to address identified priorities. Self-help groups have been shown to empower poor women from low and middle income countries financially, socially and politically [36]. Qualitative studies suggest that self-help groups work through building social cohesion and self-efficacy, which contribute to health-enhancing behavioural change at community level [37].

Both our trial design and analysis strategy have multiple strengths. AMETHIST is the first cluster randomised trial of a risk differentiated, need-based and targeted intervention for HIV prevention and treatment among female sex workers in Africa. The cluster randomised design facilitates the simultaneous estimation of the intervention impact on both HIV-negative and positive women. The research participants contributing to primary endpoint analysis will be recruited through RDS surveys within trial clusters, as in our previous ‘SAPPH-IRe’ trial. RDS reduces sampling bias and improves representativeness of ‘hard-to-reach’ populations by limiting the number of referrals any one respondent can have creating ‘deep’ rather than ‘wide’ sample networks [31]. We have outlined our RDS implementation in advance, described potential biases related to the use of RDS design in practice, attempted to collect information vital to signal whether potential biases exist, and planned sensitivity analyses to quantify their impacts on our findings.

Our design has also limitations: a longer trial would have been preferred. To minimise contamination between FSW communities/spill-over effect, we used 22 clusters, which might compromise the power of the study. However, our study is larger than previous clustered randomised trials of similar interventions in Africa [10]. We also sought to strengthen power by using restricted randomisation based on key characteristics of FSWs to maximise the chance of baseline balance.

Pragmatic trials that aim to evaluate the success and effectiveness of complex interventions pose particular challenges. One such challenge is how best to characterise the interventions under study and their hypothesised mechanism of action. This is essential so that interventions can be replicated, users of the research findings know what would be necessary to implement the intervention in other settings, and the generalisability of the findings can be considered. We combined aspects of the TIDIER and Proctor frameworks to provide a structured description of the intervention. In addition, we explicitly delineate each step through which we anticipate our intervention components will lead to measurable change, which we will test through a process evaluation conducted throughout the trial. Using mixed methods, we will formally document the intervention’s fidelity to design, feasibility of delivery and acceptability to the intended target audience as well as contextual factors that may have affected its implementation and effectiveness.

Another challenge for our trial design has been in deciding on the most appropriate primary endpoint and how this will be measured. We have proposed a composite endpoint including data on four domains that together reflect the risk of a woman (either HIV positive or negative) being involved in HIV transmission/acquisition. The use of this composite endpoint poses both conceptual and methodological challenges. Composite endpoints are commonly used in clinical trials, including in HIV [38], with the most common reason being that this can increase statistical power. However, difficulties in interpretation are recognised. The multiple outcomes included within a composite endpoint may differ in their importance to clients and providers, may differ in their absolute frequency and may experience different risk reductions as a result of the intervention, and all of these effects influence interpretation [39]. While we do not currently have available population level data among FSW data on the outcome as we will measure it in the trial, we do have similar data from previous RDS surveys, when either 22.0% [10] (no drug levels or verification of reported condom use) or 28.4% [7] (no drug levels but STI test results available) of FSW were positive for our primary outcome, which the intervention seeks to reduce. We anticipate the prevalence of the actual outcome will be higher if validation of self-reports of PrEP and condom use are included. In both scenarios, approximately twice as many women who could be beneficially affected by the intervention are HIV-negative than are HIV positive likely reflecting the stage of the epidemic in Zimbabwe where although there have been considerable gains in terms of treatment coverage, the rate of new infections has remained relatively static [40]. Optimising coverage and continuation of PrEP in AMETHIST sites has the potential to impact our primary outcome.

The key methodological challenge relates to the validity of self-reported data on sexual activity, condom use and uptake/adherence to medications. Our approach assumes that the likelihood that people will report *not* using PreP and/or *not* using condoms when they actually are doing so is low, and so we assign such people as at risk of HIV transmission on the basis of their self-reports. However, for those who report these protective behaviours, our approach is to collect additional information for these individuals to be classified as *not at risk.*

## Trial status

Protocol version 1.4 on 19 February 2020. Data collection from the sites will take place starting from October 2021 and will be completed 31 December 2021.
